### Tools employed in the evaluation of the variables

Test For The Evaluation Of Everyday Cognition (PECC)" [17]: measures the ability of older people to solve 12 real situations grouped into the following areas: medication, administrative management, financial management, meal preparation, transport and shopping, thus allowing to know the functional capacity of their daily life. The administration time is 35 minutes.The Montreal Cognitive Assessment Test (MoCA test) Version 8.3 [18]: allows the detection of mild cognitive impairment (MCI) by assessing executive functions, attention, abstraction, memory, language, visual-constructive abilities, calculation and orientation. The administration time is 10 minutes. The maximum score is 30 points, below 26 points being the cut-off for MCI (in developed countries).Yesavage Geriatric Depression Scale [19]: questionnaire for depression screening in people over 65 years of age. Administration time is 5 minutes. A score above 5 shows moderate depression and above 10 shows severe depression.Functional Independence Measure (FIM)" [20]: measures the level of functionality and assistance given by the caregiver. It assesses activities of daily living subdivided into motor and cognitive dimensions. Each of the 18 items has a maximum score of 7 and a minimum score of 1, making a total of 126 items."FRAIL frailty scale" [21]: provides a quantitative measure of frailty in geriatric patients. The maximum score is 5 points."Lawton and Brody Scale" [22]: designed to assess autonomy in instrumental activities in the elderly population. It takes 4 minutes to administer and is scored 0 or 1 for each of the items, with a total score of 8."ARMS-e Questionnaire" [23]: analyses in a multidimensional way the lack of adherence in multi-pathological patients, allowing individualised assessment of the barriers detected in adherence problems."Medical Outcomes Study (MOS) Questionnaire" [24]: allows us to quickly and simply assess social support in a global manner, but also allows us to ascertain the emotional, instrumental, affective and positive social interaction dimensions.

An individual data collection sheet will be used for each participant and recorded in a database designed specifically for this study.

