## Material and methods

### Design and setting of the study

An experimental, prospective, randomised, parallel-controlled, clinical trial will be carried out with two arms of fixed allocation with an experimental group and a control group. It will be conducted for one year at the University of Salamanca (Spain) in eleven municipal centres and associations for the elderly belonging to the Salamanca City Council. Participants belonging to the occupational therapy programmes of the Geriatric Revitalisation Project organised by the University of Salamanca, aged 60 years or older without cognitive impairment at the time of inclusion, will be recruited.

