### Sample/Participants

#### Participants

The study population will be composed of people aged 60 years or older without cognitive impairment who voluntarily agree to participate in the Occupational Therapy programme of the Geriatric Revitalisation project organised by the University of Salamanca in collaboration with the Salamanca City Council (Spain), within the framework of the Research in Active Ageing agreement. Regarding the location, the study will be carried out in eleven municipal centres and associations for the elderly belonging to the Salamanca City Council, Spain. The researchers of the University of Salamanca will invite older adults to participate in the study by explaining the details of the clinical trial and they can be included once they have given their verbal and written consent and meet the following selection guidelines: (A) Inclusion criteria: Being 60 years of age or older, voluntarily signing the informed consent form authorising participation and completing the initial assessment. (B) Exclusion criteria: Not having knowledge of reading and writing or significant deficits in language comprehension, being institutionalised, to have a clinical diagnosis of a neurocognitive disorder included in the DSM-V at the time of the initial assessment and participating in another cognitive stimulation programme. (C) Withdrawal criteria: Dropping out of the programme.

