#### Description of the variables

The primary variable will be everyday cognition, measured by the Test for the Evaluation of Everyday Cognition (PECC) and cognitive performance, measured by the Montreal Cognitive Assessment Test (MoCA). Secondary variables will be functionality (Functional Independence Measure, FIM), emotional state (Yesavage Scale), frailty (Frailty Index) and independence in instrumental activities of daily living (Lawton and Brody Scale). We will also record the following intervening variables in the clinical history of each participant: social support (Questionnaire MOS) and adherence to treatment (Questionnaire ARMS-e), and other socio-demographic data (age, sex, level of education, marital status and main occupation).

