### Data analysis

To test the normal distribution of data, a histogram will be used. Variables that have a normal distribution shall be defined by the mean and standard deviation, while variables that do not follow a normal distribution shall be defined by the median and the interquartile range. The effects of the intervention on primary outcomes (everyday cognition and cognitive function) and secondary outcomes (functionality, emotional state, and fragility) will be examined through a two-way analysis of covariance (ANCOVA), with the intervention group (control or experimental) included as a fixed factor. The differences between initial results and those after intervention, as both the dependent variable and covariates, will include intervening study variables such as age, gender, education level, marital status and occupation. The difference in means will be calculated using Cohen’s d to evaluate effect size. Group differences in intervening variables will be analyzed using independent samples t-tests for continuous variables (e.g., age). The chi-square test will be used to investigate group differences in categorical variables (e.g. gender). Significant values will be considered for p-values less than 0.05, with a 95% confidence interval. IBM SPSS Statistics software version 28.0.1 will be used for statistical analysis”.

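### MoCA as a primary change outcome risks a ceiling effect in people described as unimpaired; its size is unknown, and adjusting for baseline MoCA and reporting ceiling rates would limit misreading

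*Protocol article*

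**What the plan says.** Under Description of the variables, the Protocol article gives two primary variables: everyday cognition (PECC) and "cognitive performance, measured by the Montreal Cognitive Assessment Test (MoCA". The Data analysis section repeats this: "The effects of the intervention on primary outcomes (everyday cognition and cognitive function".

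Under Tools employed in the evaluation of the variables, MoCA is presented as a screening instrument that "allows the detection of mild cognitive impairment (MCI) by assessing executive functions, attention, abstraction, memory, language" and other functions. On its range the text says: "The maximum score is 30 points, below 26 points being the cut-off for MCI (in developed countries".

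Design and setting of the study describes the population as people "aged 60 years or older without cognitive impairment at the time of inclusion". The Participants section puts this into practice without a MoCA score. Inclusion requires "Being 60 years of age or older, voluntarily signing the informed consent form authorising participation and completing the initial assessment". Impairment is excluded through a diagnosis: "to have a clinical diagnosis of a neurocognitive disorder included in the DSM-V at the time of the initial assessment".

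The Data analysis section plans an ANCOVA with the difference between initial and final results as the dependent variable. The covariates it names are age, gender, education level, marital status and occupation. Baseline MoCA is not among them.

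**The concern.** A test built to detect impairment is used to measure improvement in people described as unimpaired. By the protocol's own cut-off such people occupy the top five values of the scale, 26 to 30. Someone who starts at 30 and improves still scores 30 and enters the analysis as no change.

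Both arms receive active training, and the hypothesis under Aim is that the experimental programme adds to the benefit of traditional stimulation. The contrast sought is therefore largely one of extra gain, which is where the cap acts. If many participants are near 30, the difference in MoCA points will be smaller than the difference in underlying ability. A small or null result could then be read as no added effect on cognitive function, when the scale had little room to show one.

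An analysis of change that does not adjust for baseline MoCA also ignores how much room each person had. A chance difference between arms in baseline position would feed into the comparison.

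**Working it through.** **Inputs from the protocol.** Maximum 30; MCI below 26; no MoCA threshold for entry; analysis of pre-post difference. The protocol gives no MoCA baseline mean, SD, measurement error, expected change or ceiling rate. The sample size rests on everyday cognition, so there is no MoCA figure of the plan's own to reproduce.

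**Step 1: room to improve.** For a person at 26 or above, maximum gain = 30 − 26 = 4. If baselines were spread evenly over 26 to 30, average room = (4 + 3 + 2 + 1 + 0)/5 = 2 points. A person below 26 has more than 4 points, and the eligibility criteria admit such a person if no disorder has been diagnosed.

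**Step 2: how much of a true difference is recorded.** Simulation: observed score = round(true score + error), capped at 30. Share retained = observed between-arm difference ÷ true difference.

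First set of assumptions: true-score SD 2 or 3; error SD 1.5; a true difference of 1 or 2 points gained, or 1 point of decline avoided.

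| True-score mean | Gain, no entry floor | Gain, all at 26 or above | Avoided decline, no floor | Avoided decline, all at 26 or above |
|---|---|---|---|---|
| 22 | 0.980–0.999 | 0.880–0.986 | 0.994–1.000 | 0.963–0.997 |
| 24 | 0.930–0.986 | 0.798–0.954 | 0.974–0.995 | 0.921–0.984 |
| 26 | 0.813–0.919 | 0.675–0.868 | 0.910–0.964 | 0.840–0.940 |
| 28 | 0.615–0.725 | 0.510–0.679 | 0.772–0.842 | 0.706–0.813 |

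The no-floor columns match eligibility as written. Average room there is 2.3 to 8.0 points; with everyone at 26 or above it is 1.4 to 3.3.

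Second set: true-score SD 2; error SD 1.2; gains 0.39 and 1.39, so a true difference of 1.00. (The 0.39 is the control-arm gain in everyday cognition under Sample size; using it for MoCA is an assumption.)

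- All at 26 or above, means 26 / 27 / 28: observed difference 0.85 / 0.76 / 0.63, a loss of 15% to 37%.
- No floor, means 25 / 26 / 27 / 28: 0.96 / 0.91 / 0.82 / 0.68, a loss of 4% to 32%.
- All at 26 or above: 24% to 48% already score 29–30 at baseline, and 50% to 73% of the experimental arm do so at the end.

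**Step 3: standardised terms.** The cap shrinks the SD as well as the difference. In the second set, Cohen's d for the change score falls by 9% / 14% / 22% with the floor and by 5% to 22% without it. With baseline adjustment the falls are about 7% to 16% and 3% to 15%. Part of each fall is rounding, not the cap.

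**Step 4: what baseline adjustment gives.** Compare Var(final − baseline) with Var(final) − Cov(final, baseline)²/Var(baseline). In large samples the second is never larger. Over the settings tried it was about 5% to 28% smaller, depending on the assumed means and errors.

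**The case against.** The strongest reply is that 26 is a property of the instrument and not an entry rule. Eligibility defines unimpaired as having no clinical diagnosis, so people scoring below 26 can be enrolled without any contradiction. If the true-score mean were 22 to 24 with no floor, 93% to 100% of the true difference would be recorded. That stands, and it is why a reader should not infer that the whole sample has at most 4 points of room.

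Second, the Background also speaks of maintaining cognition. The scale is open downwards, so avoided decline is less affected: 96% retained against 92% for a gain, at mean 26, SD 2, no floor. A reader might infer that any benefit is understated, but the protocol does not support that.

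Third, under randomisation the cap does not bias the mean difference in observed MoCA points. It reduces sensitivity relative to an underlying ability that the protocol never defines. This also stands, and with the smaller standardised losses it means the cost in power is modest. What remains is the risk of misreading a small or null difference.

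Fourth, Tobit and proportional-odds models carry assumptions of their own, so there is no compelling reason to replace the mean difference as the main estimate. Accepted.

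Finally, ceiling reporting is often left to an analysis plan, which is not shown. But the article itself fixes the outcome, the population, the dependent variable and a list of covariates without baseline MoCA. The sentence on covariates is loosely worded; if baseline scores were meant, the first part of the fix is only a clarification.

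**Conclusion.** The point holds as a risk of unknown size. MoCA is a primary outcome capped at 30, the population is described as unimpaired, and the planned model takes the pre-post difference without naming baseline MoCA as a covariate. Those scoring 26 or more can gain at most 4 points; others may have more room.

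Under the assumptions shown, understatement of a gain runs from almost none to about half in raw points (49%, at mean 28 and SD 3 with everyone at 26 or above). It is smaller in standardised terms, at most about 22% in the settings where that was computed. All these figures rest on assumed means, SDs and errors. None is an estimate for this trial.

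The finding concerns MoCA only. The article states no score range for PECC, so no ceiling can be shown for the other primary outcome or for the sample size built on everyday cognition.

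**What to change.** In the Data analysis section:

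1. Analyse the final MoCA score with baseline MoCA as a covariate, in place of the pre-post difference without it. Keep the adjusted mean difference as the main estimate. Baseline is measured before randomisation, so it is a valid covariate.
2. Add a proportional-odds (or Tobit, censored at 30) model as a sensitivity analysis.
3. Report, by arm, the share at or near 30 (for example 29–30) at baseline and at the end.
4. State in advance that a null MoCA difference will be read in light of those shares and not as proof of no effect on cognitive function.

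No new visits, tests or participants are needed. The baseline adjustment uses a score already collected and improves precision. The only downside is one extra, less familiar analysis to report beside the mean difference.

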#### Interventions

Two parallel intervention programmes will be designed, coinciding with the two study groups: a training programme in everyday cognition (experimental group) and a traditional cognitive stimulation programme (control group). These programmes will be previously structured and supervised by the team of researchers from the University of Salamanca who form the Geriatric Revitalisation project within the framework of the Research in Active Ageing (PreGe) agreement. The interventions will be carried out on a face-to-face basis in the eleven centres or associations of elderly people in the same city, which voluntarily participate in the Occupational Therapy programme taught by the main researcher of the study. Each centre will have a weekly intervention session for 7 months, completing 25 sessions. The duration of each session will be 50 minutes.

The working technique will be group work, but the activities to be carried out will be individual. The parts of a standard session will be: 10 minutes for the presentation of the session and the explanation of the activity by the researcher, 30 minutes to carry out the activity individually and the last 10 minutes for the correction of the activities, farewell and final feedback. The rooms in the senior citizens’ centres where the interventions will be carried out will be similar in terms of infrastructure, being in all cases a suitable environment for the optimal development of the intervention sessions.

As we have pointed out, although the number and duration of the sessions will be the same in both groups, the intervention to be carried out will be different in each study group and the participants will not know to which group they belong:

The training programme in everyday cognition will be carried out with the experimental group. For this intervention, materials will be designed and used that are as similar as possible to those that the older adult might encounter in everyday tasks or when facing the resolution of different problems that may arise in their daily lives; with the ultimate goal of bringing the intervention closer to the real life of the participants. In these tasks, participants must make use of cognitive functions such as attention, reasoning, working memory, planning or processing speed, during the development of instrumental activities of daily life such as: meal preparation, housekeeping, use of transport, shopping, use of the telephone, medication, financial management and access to information and current affairs. The proposed activities include context and significance, as they are problems or actions that the person must solve in their daily life in order to maintain their personal autonomy and independence, in order to be able to live in society. Currently, there is little information in our country about training in everyday cognition. The study carried out by Sánchez et al. in 2019 [25] and the one published by the same authors in 2021 [26], which introduce practical examples of typical sessions, have been taken as a reference for the creation of a training booklet on everyday cognition. We can observe in the first annex to S5, one of these training activities in everyday cognition. In this case, training in medication taking and adherence to treatment will be worked on. In the activity, a practical scenario is explained in which Marisa (fictitious person) has gone to the doctor and has been given a leaflet that she has to read and understand in order to answer the questions correctly. In the second task, participants have to read, understand and memorise a medication leaflet and answer some questions without rereading the information on the leaflet.The traditional cognitive stimulation programme will be carried out with the control group. Tasks focused on specific cognitive functions such as attention, memory, orientation, praxis, calculation, visual perception, executive functions and reasoning will be carried out. For the creation of the cognitive stimulation notebook, reference was made to the study by Calatayud et al. in 2020 [27], who used a "neuronal activation" notebook. The cognitive training notebook includes cards in paper format, where each of the cognitive functions mentioned above are worked on. An example of this is the sample session shown in the second annex of S5, in which attention is worked on by describing what is observed in an image, and then participants are asked to answer questions about it.

You can see an example of a session in the document (S5 File).

### Data analysis

To test the normal distribution of data, a histogram will be used. Variables that have a normal distribution shall be defined by the mean and standard deviation, while variables that do not follow a normal distribution shall be defined by the median and the interquartile range. The effects of the intervention on primary outcomes (everyday cognition and cognitive function) and secondary outcomes (functionality, emotional state, and fragility) will be examined through a two-way analysis of covariance (ANCOVA), with the intervention group (control or experimental) included as a fixed factor. The differences between initial results and those after intervention, as both the dependent variable and covariates, will include intervening study variables such as age, gender, education level, marital status and occupation. The difference in means will be calculated using Cohen’s d to evaluate effect size. Group differences in intervening variables will be analyzed using independent samples t-tests for continuous variables (e.g., age). The chi-square test will be used to investigate group differences in categorical variables (e.g. gender). Significant values will be considered for p-values less than 0.05, with a 95% confidence interval. IBM SPSS Statistics software version 28.0.1 will be used for statistical analysis”.

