**Methods:**

A parallel randomised controlled clinical trial with two arms will be conducted. It will be carried out by the University of Salamanca (Spain) in eleven centres and associations for the elderly of the City Council of Salamanca. People aged 60 years or older without cognitive impairment will be recruited. Participants will be randomly distributed into two groups: the experimental group will undergo a training programme in everyday cognition and the control group a programme of traditional cognitive stimulation, completing 25 sessions over 7 months. All participants will be assessed at the beginning and at the end of the intervention, where socio-demographic data and the following scales will be collected: The Medical Outcomes Study (MOS), Questionnaire ARMS-e, Everyday Cognition Test (PECC), Scale Yesavage, Test Montreal Cognitive Assessment (MoCA), The Functional Independence Measure (FIM), Fragility Index and Lawton y Brody Scale.

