#### Randomisation

Participants voluntarily enroll in one of the eleven groups that belong to different senior centers to receive one of two types of cognitive intervention. In order to ensure the greatest fairness among the different groups, a maximum of 15 and a minimum of 5 participants per group were established. Following recruitment, randomization will be carried out through simple allocation of each group belonging to each senior group by using the Epidat 4.2 program. The eleven intervention groups will be allocated to either the experimental or control group as detailed in Fig 1 of the SPIRIT 2013 registration, interventions and assessments program.

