#### Blinding

The work of sequencing, randomisation, recruitment and allocation of the senior centres to each group (experimental or control) will be completed by research staff not involved in the evaluations or interventions of each group, which will avoid possible biases in the study.

The participants will also be blinded on the hypothesis and expectations of the study. In order to minimise any contamination between groups, the evaluation process will be carried out by external research staff who will carry out the measurements, previously educated and trained; with the aim of avoiding subjective biases in the process, as they will be unaware of the intervention group to which each elderly centre is assigned, so that the clinical trial will have a masking of blind evaluation by third parties. In addition, the researchers responsible for the statistical analysis of the study will be blinded, with the intention of increasing the rigour of the study process, thus increasing the scientific quality.

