### Procedures and data collection

#### Evaluations and study plan

Participants will be assessed at two points during the study: the baseline assessment at the beginning of the study and the final assessment after the end of the intervention. The baseline assessment will take place after recruitment and before randomisation and allocation of subjects to the corresponding group. This initial assessment includes the recording of the independent variables and the primary outcome variables to be studied; the intervening variables will be recorded and several objective assessment tests will be used. Then, after randomisation, the intervention for each group will be carried out. Then, another assessment will be carried out, considered the final assessment, where participants will be asked to complete the same objective tests as in the initial assessment. The results will be notified by means of an individual and personal report to those persons who expressed the wish at the beginning to receive the information corresponding to the results and evolution. All evaluations will be carried out by research staff, previously trained and instructed in this process. This process can be seen in more detail in Fig 2 which includes a flow chart of the study methodology.

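### Eleven intact groups are randomised, but the ANCOVA treats participants as independent, so p-values are too small and confidence intervals too narrow whenever outcomes correlate within groups

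*Protocol article*

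**What the plan says.** The only allocation mechanism described works on groups. According to the Randomisation section, "Participants voluntarily enroll in one of the eleven groups that belong to different senior centers", with "a maximum of 15 and a minimum of 5 participants per group were established". After recruitment, "randomization will be carried out through simple allocation of each group belonging to each senior group by using the Epidat 4.2 program". The section then states: "The eleven intervention groups will be allocated to either the experimental or control group". The Blinding section agrees: it is the senior centres that are allocated, and assessors are kept unaware of each centre's arm.

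Two other places read as if individuals were randomised. The abstract's Methods say "Participants will be randomly distributed into two groups". Evaluations and study plan places the baseline assessment "before randomisation and allocation of subjects to the corresponding group". Neither gives an individual-level procedure.

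Under Data analysis, the primary and secondary outcomes "will be examined through a two-way analysis of covariance (ANCOVA), with the intervention group (control or experimental) included as a fixed factor". The covariates are age, gender, education, marital status and occupation. Significance is judged at p below 0.05 with 95% confidence intervals. No group or centre term, random effect, cluster-robust variance or group-level summary is mentioned.

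**The concern.** When intact groups are allocated, the arm comparison is a comparison between groups, and its error must include the variation between groups. A person-level ANCOVA leaves that component out. There are two reasons to expect it to be above zero here: members select their own centre, and each centre then shares its weekly sessions for seven months, including joint explanation, correction and feedback.

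The consequence runs in one direction. With any positive ICC the standard error is understated, the 95% intervals cover less than 95%, and the trial is more likely than its nominal rate to declare a difference that does not exist. This affects both primary outcomes and every secondary comparison made with the same model. Because the article fixes a specific model that conflicts with its own allocation scheme, this is more than a detail left to a later document.

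**Working it through.** **Inputs from the protocol**
- 11 groups, each of 5 to 15 people (Randomisation).
- 99 participants and 20% expected loss (Sample size): 99 × 0.80 ≈ 79 evaluable, and 79 / 11 = 7.18 per group.
- One-sided planning at 95% confidence (Sample size). The Data analysis threshold of 0.05 does not state sidedness, so both are shown.

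**Assumed:** the ICC, which the protocol does not give. The range used is 0.01 to 0.20.

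**Formulas**
- Design effect: DE = 1 + (7.18 − 1) × ICC.
- True two-sided error of the nominal 5% test: 2 × [1 − Φ(1.96 / √DE)].
- True one-sided error: 1 − Φ(1.645 / √DE).
- Shortfall in interval width: 1 − 1 / √DE.
- Effective sample size: 79 / DE.

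At ICC 0.05, DE = 1 + 6.18 × 0.05 = 1.31 and √DE = 1.144. The two-sided error is 2 × [1 − Φ(1.713)] = 0.087.

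| ICC | DE | Two-sided error | One-sided error | Interval too narrow by | Effective N of 79 |
|---|---|---|---|---|---|
| 0.01 | 1.06 | 5.7% | 5.5% | 3% | 74 |
| 0.05 | 1.31 | 8.7% | 7.5% | 13% | 60 |
| 0.10 | 1.62 | 12.3% | 9.8% | 21% | 49 |
| 0.20 | 2.24 | 19.0% | 13.6% | 33% | 35 |

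**Sensitivity to group size.** Without loss there are 99 / 11 = 9 per group. DE is then 1.08, 1.40 and 1.80 at ICC 0.01, 0.05 and 0.10, and the two-sided error is 5.9%, 9.8% and 14.4%.

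**Simulation**
- 11 groups of 9, split 6:5, 40,000 runs per ICC: the person-level test rejected in 6.0%, 10.1% and 14.3% of null trials at ICC 0.01, 0.05 and 0.10. A t-test on the 11 group means (11 − 2 = 9 degrees of freedom) stayed between 4.9% and 5.1%.
- Unequal groups of 5 to 15, 20% loss and simple allocation, 6,000 runs per setting: the person-level test gave 6.0%, 9.6% and 14.1%, and the group-level t-test 4.6% to 5.5%.

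**Power.** The planned 99 cannot be reproduced because no standard deviation (SD) is stated. Working back from a difference of 2.57 − 0.39 = 2.18, one-sided 5%, 80% power and 99 × 0.80 / 2 = 39.6 completers per arm gives SD = 2.18 × √(39.6 / 2) / (1.645 + 0.842) = 3.90. With that SD, 79 completers and a one-sided test on 9 degrees of freedom, power is about 64% at ICC 0.05 and 56% at ICC 0.10.

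**Could the model already contain the group?** The ANCOVA is called two-way, but no second factor is named. If that factor were centre as a fixed effect, it would be nested within arm and the arm effect could not be estimated separately.

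**The case against.** The strongest objection is that the size of the error rests entirely on an assumed ICC. At 0.01 the inflation is under one percentage point. The outcome is a pre-post change adjusted for personal characteristics, which may remove some stable differences between centres. The activities are done individually for 30 of the 50 minutes, the rooms are similar, and the principal investigator delivers the sessions, so differing therapists do not add variation. All of this is fair and argues for the lower part of the range. It does not make the ICC zero, because self-selection into centres and shared sessions remain, and the direction of the error does not depend on its value.

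Three points of precision also stand:
- The two-sided rates count false differences in both directions. Half of each favours the everyday-cognition arm (2.9%, 4.3% and 6.2% at ICC 0.01, 0.05 and 0.10), to be compared with 2.5%. If the test is one-sided at 5%, the rates to compare with 5% are 5.5%, 7.5% and 9.8%.
- Eleven groups fix the degrees of freedom. They do not reduce the information to 11 observations, as the effective sample sizes show.
- The t-tests and chi-square tests in the same section compare participant characteristics, so they do not affect inference on the intervention.

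An unseen analysis plan does not answer the point, since the article itself commits to a model that does not match its design.

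**Conclusion.** The analysis is wrong as written and needs correcting before the data are analysed. The trial randomises 11 groups, and the stated ANCOVA gives valid inference only if the within-group correlation is zero. Over ICCs of 0.01 to 0.10, with 79 evaluable participants in groups of equal size, the true two-sided type I error is about 6% to 12% against a nominal 5%, and the intervals are about 3% to 21% too narrow. Unequal group sizes push the error somewhat higher. That the error is understated for any positive ICC is certain. How far depends on an ICC that the protocol does not provide.

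**What to change.** 1. State once that the group (centre) is the unit of randomisation, and bring the abstract and the Evaluations and study plan section into line with the Randomisation and Blinding sections.
2. Replace the ANCOVA with a linear mixed model: arm as a fixed effect, the planned covariates, a random intercept for group, and Satterthwaite or Kenward-Roger degrees of freedom. Ordinary sandwich standard errors without a small-sample correction are not reliable with 11 groups.
3. Support it with a permutation test at group level, or a t-test on the 11 adjusted group means with 9 degrees of freedom.
4. State whether the tests are one-sided or two-sided, report the observed ICC, and follow the reporting extension for cluster-randomised trials.

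The cost is rewording and a different procedure in the same software, with wider intervals that have their stated coverage. Validity needs no extra participants. Power is a separate matter: the Sample size section mentions no design effect, so the protocol should add one or state openly the power that 11 groups can deliver.
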